### Process evaluation

A process evaluation will be conducted by an LICTR researcher in accordance with MRC guidance on evaluating process in complex interventions [19]. In brief, the aims of this evaluation will be to (1) examine the uptake, delivery and acceptability of the optimisation intervention across local authorities/children’s centres (reach); (2) explore the effects of individual intervention components at increasing parent engagement, along with potential unintended consequences; and (3) consider the utility of theories underpinning the intervention and approach used to develop the intervention design. Process measures will include quantitative measurement of centre uptake and fidelity of delivered trial components; qualitative and quantitative analysis of stakeholder perceptions of intervention components considering individual, organisational and contextual factors; quantitative measurement of enrolment methods used to recruit HENRY programme participants; and qualitative and/or quantitative measurement of predicted behaviour change outcomes among stakeholders targeted in the implementation optimisation. Quantitative data required for process evaluation will be gathered and reported on paper case report forms by a researcher within the LICTR, who will also collect qualitative data from a random selection of sites in person, including interviews and observations.

### Economic evaluation

Economic evaluation will model the benefits of optimisation intervention over the costs of implementation and will seek commissioners’ willingness to pay for this. It will include the costs required to deliver the intervention (gathered and transferred from HENRY) and the routinely collected outcome data.

The cost-effectiveness analysis in the present trial will include an array of trial endpoints (including parent enrolment and attrition rates) and costs. Cost-effectiveness acceptability curves will describe the probability that the optimisation intervention is cost-effective for a range of maximum monetary values that a decision-maker might be willing to pay for a particular unit change in outcome. Cost-effectiveness analysis leaves it to decision-makers to form their own view of the relative importance of these results [54]; therefore, in a second part of the work, we will conduct a meeting with commissioners to determine their willingness to pay per additional unit of effectiveness (parent engagement) before concluding whether the optimisation intervention can be considered cost-effective. We will use contingent valuation techniques and design an experiment to estimate the point at which commissioners consider that the costs of the programme are acceptably offset by the benefits of engaging effectively with parents.

### Sample size

We assumed that 25% of the 32 local authorities currently running HENRY will not be eligible or will opt out of the study, leaving 24 local authorities (12 per arm). Power calculations for this fixed sample size (with all eligible centres in the United Kingdom invited to take part) were therefore conducted to examine anticipated power for various intervention effects, at the 5% significance level, in each of the primary outcomes and for the composite endpoint (enrol at least eight parents per programme and retain ≥75% of parents attending five of eight sessions) (see Table 1 for scenarios). On the basis of data from previous HENRY programmes (all terms in 2014), we assumed an average of 6 children’s centres per local authority providing a total of 144 children’s centres (72 per arm), an intra-cluster correlation coefficient (ICC) between 0.05 and 0.1, a coefficient of variation in cluster size of 0.54, and the following estimates of the outcomes in the control sites (HENRY alone): 55% of centres will enrol at least eight parents per programme; 50% of centres will retain ≥75% of parents attending five of eight sessions; and 25% of centres will enrol at least eight parents per programme and retain ≥75% of parents attending five of eight sessions. Thus, with the anticipated number of centres (24 local authorities, 144 children’s centres), we will have at least 80% power to detect meaningful improvements in differences of between 25% and 30% in either of the primary endpoints or the composite endpoint at the 5% significance level, assuming the ICC is no greater than 0.05.

**Table 1 Tab1:** Power calculations for enrolment and attrition endpoints for various estimates of the intervention effect and a fixed sample size of 144 children’s centres in 24 local authorities

Outcome in the control	Percentage point increase in intervention	Power for ICC = 0.1	Power for ICC = 0.05
Enrolment (≥8 parents per programme)			
55%	5%	6%	7%
	10%	15%	18%
	15%	29%	35%
	20%	49%	58%
	25%	70%	79%
	30%	87%	93%
Attrition (≥75% of parents attending five of eight sessions)			
50%	5%	6%	7%
	10%	15%	17%
	15%	28%	34%
	20%	47%	55%
	25%	67%	76%
	30%	84%	91%
Enrolment and attrition (at least eight parents per programme and 75% of parents attending five of eight sessions)			
25%	5%	7%	8%
	10%	17%	19%
	15%	31%	37%
	20%	49%	58%
	25%	67%	76%
	30%	82%	89%

*ICC* Intra-cluster correlation coefficient

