**Methods/design:**

The Optimising Family Engagement in HENRY (OFTEN) trial is a cluster randomised controlled trial being conducted across 24 local authorities (approximately 144 children’s centres) which currently deliver HENRY programmes. The primary outcome will be parental enrolment and attendance at the HENRY programme, assessed using routinely collected process data. Cost-effectiveness will be presented in terms of primary outcomes using acceptability curves and through eliciting the willingness to pay for the optimisation from HENRY commissioners. Secondary outcomes include the longitudinal impact of the optimisation, parent-reported infant intake of fruits and vegetables (as a proxy to compliance) and other parent-reported family habits and lifestyle.

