## Methods/design

### Design

This study is a two-arm, multi-centre cRCT across 24 local authorities (local governments) (supporting approximately 144 children’s centres) in the United Kingdom to determine the effectiveness and cost-effectiveness of an optimisation intervention to promote parent engagement in the HENRY programme compared with standard HENRY practice (Fig. 1). Although the children’s centres deliver the HENRY programme, owing to the multi-component and interactive nature of the optimisation intervention, local authorities will be the units of randomisation (i.e., clusters) to prevent contamination between the randomised groups. Outcomes will be assessed through routinely collected data available for each HENRY programme at the parent and children’s centre levels. Information on commissioners’ willingness to pay (within local authorities) related to the optimisation intervention will be elicited. A process evaluation will be conducted alongside the cRCT in accordance with the MRC guidance on evaluating process in complex interventions [19].

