### Setting

The study will be conducted in local authorities with children’s centres where staff are currently trained to deliver the HENRY programme. There are currently 32 local authorities (approximately 144 centres) in the United Kingdom running the programme, all of which provide process data to the central HENRY office for monitoring/quality assurance (QA) purposes. These data will be anonymised and transferred for analysis.

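### About 144 children's centres are attributed both to all 32 local authorities and to the 24 expected to take part; at least one count is wrong, and if it is the trial count, Table 1 is too favourable

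*Protocol article*

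**What the plan says.** Four places in the protocol article give a centre count.

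- **Setting:** "There are currently 32 local authorities (approximately 144 centres) in the United Kingdom running the programme". It adds that all of them send process data to the HENRY central office.
- **Abstract, Methods/design:** the trial is "being conducted across 24 local authorities", with about 144 centres in parentheses.
- **Design:** the trial runs "across 24 local authorities (local governments) (supporting approximately 144 children’s centres".
- **Sample size:** "We assumed that 25% of the 32 local authorities currently running HENRY will not be eligible or will opt out of the study", which leaves 24 (12 per arm). The section then takes "an average of 6 children’s centres per local authority providing a total of 144 children’s centres (72 per arm". The caption of Table 1 repeats 144 centres in 24 authorities.

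The mean of 6 is introduced with "On the basis of data from previous HENRY programmes (all terms in 2014". The same sentence supplies "an intra-cluster correlation coefficient (ICC) between 0.05 and 0.1", "a coefficient of variation in cluster size of 0.54" and the control rates of 55% (enrolment), 50% (attrition) and 25% (both together). The section concludes that power is at least 80% for differences between 25 and 30 points if the ICC does not exceed 0.05.

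**The concern.** The same total describes the pool before the assumed 25% loss of authorities and the trial after it. In Setting, 144 over 32 is 4.5 centres per authority. In Sample size, 144 over 24 is 6. The two agree only if the eight authorities that drop out bring essentially no centres with them. The protocol does not say this, and Setting describes all 32 as currently running the programme. The gap is too wide for the word approximately to cover: it is 144 against 192 for the whole pool, or 108 against 144 for the trial.

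Every cell of Table 1 is computed for 144 centres. If the trial holds nearer 108, the table is too favourable, and a null result would be judged against more power than the design had.

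**Working it through.** **Inputs.** From Sample size: 12 authorities per arm; mean centres per authority m = 6; coefficient of variation (CV) 0.54; ICC 0.05 or 0.10; control rates 55%, 50% and 25%. From Analysis: two-sided 5% level. From Setting: 144 centres in 32 authorities.

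**The counts**

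- Sample size: 32 × 0.75 = 24; 24 × 6 = 144; 144 / 2 = 72 per arm. At 6 each, 32 authorities would hold 32 × 6 = 192.
- Setting: 144 / 32 = 4.5. At 4.5 each, 24 authorities hold 24 × 4.5 = 108, or 54 per arm.

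**Formulas**

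- Design effect: DE = 1 + ((CV² + 1)m − 1) × ICC, with CV² + 1 = 1.2916.
- Effective centres per arm: n = 12m / DE.
- Power: the normal two-proportion formula, with pooled variance under the null.

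**Reproducing Table 1 (m = 6)**

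- ICC 0.05: DE = 1 + (7.7496 − 1) × 0.05 = 1.3375; n = 72 / 1.3375 = 53.8.
- ICC 0.10: DE = 1.675; n = 72 / 1.675 = 43.0.
- Example, enrolment 55% to 80% at ICC 0.05. Null standard error √(2 × 0.675 × 0.325 / 53.83) = 0.0903. Alternative standard error √((0.2475 + 0.16) / 53.83) = 0.0870. z = (0.25 − 1.96 × 0.0903) / 0.0870 = 0.84, so power is 79.9% (printed 79%).

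All 36 printed cells are reproduced within 1.4 points. Table 1 is therefore computed correctly for 24 authorities of 6 centres.

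**Same formulas with m = 4.5**

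- ICC 0.05: DE = 1 + (5.8122 − 1) × 0.05 = 1.2406; n = 54 / 1.2406 = 43.5.
- ICC 0.10: DE = 1.4812; n = 54 / 1.4812 = 36.5.

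| Endpoint | ICC | +25 points: printed | +25 points: 108 centres | +30 points: printed | +30 points: 108 centres |
|---|---|---|---|---|---|
| Enrolment | 0.05 | 79% | 71% | 93% | 88% |
| Attrition | 0.05 | 76% | 68% | 91% | 85% |
| Composite | 0.05 | 76% | 68% | 89% | 83% |
| Enrolment | 0.10 | 70% | 63% | 87% | 81% |
| Attrition | 0.10 | 67% | 60% | 84% | 78% |
| Composite | 0.10 | 67% | 60% | 82% | 75% |

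Difference detectable with 80% power at ICC 0.05 (enrolment, attrition, composite):

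- m = 6: 25.0, 25.8 and 25.9 points.
- m = 4.5: 27.5, 28.4 and 29.0 points.

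**Sensitivity**

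- *Test:* a noncentral t calculation with 22 degrees of freedom also reproduces Table 1 within 2 points. For 108 centres at ICC 0.05 it gives 69.5%, 66.4% and 66.4% at 25 points, and 87.0%, 84.0% and 81.8% at 30 points.
- *CV:* if the mean is wrong, the CV from the same data may be wrong too. With an assumed CV from 0.4 to 0.7, m = 4.5 and ICC 0.05, power at 25 points runs from 72% to 69% for enrolment and from 69% to 66% for attrition and the composite. The detectable differences span 27.2 to 29.5 points.

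**The case against.** The best defence is that Sample size is coherent in itself. It applies the 25% loss to authorities, multiplies the remaining 24 by a mean credited to 2014 programme data, and gets 144. The pairing of 144 with 24 recurs in the Abstract, Design and the Table 1 caption. The pairing with 32 appears once, in an approximate parenthesis that feeds no calculation. This stands, and it rules out two stronger readings.

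- A reader might infer that the loss of authorities never reached the centre count. It did: without it, 6 per authority would have given 192.
- A reader might infer that Table 1 overstates power. That follows only if the Setting count is right, and the document does not establish this. The Background figure of more than 150 programmes a year across 32 authorities sits somewhat more easily with 144 centres than with 192. It does not decide the matter, because the randomisation balances on the proportion of centres that ran at least one programme in 2015, so some centres may run none in a year.

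It is also fair to say that the headline power sentence survives in either case. Even with 108 centres, 80% power at ICC 0.05 is reached between 27.5 and 29 points, inside the range it names. Table 1 already prints less than 80% at 25 points.

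Centre-level exclusions add little that can be quantified. Removing the five centres used in the development phase (139 left) gives 79% and 76% at 25 points for enrolment and attrition at ICC 0.05, which matches the printed cells. The document gives no figure for opt-out by individual centres.

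The defence does not remove the conflict. Repeating one pairing more often does not show that it is the correct one.

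**Conclusion.** The contradiction is real and touches the main input to the power calculation: at least one of the two counts is wrong, and the document does not show which. The consequence is conditional.

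- **If the mean of 6 is right,** the error is confined to Setting, and Table 1 stands.
- **If Setting is right,** the 25- and 30-point cells of Table 1 are about 5 to 8 points too high. Attrition and the composite fall below 80% at ICC 0.10 even for the largest tabulated difference. At ICC 0.05, power at 30 points stays above 80% for all three endpoints.

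The second case assumes that the lost authorities are of average size, that no individual centre opts out, and that ICC, CV and control rates are unchanged. If the lost authorities are smaller than average, the trial count lies between 108 and 144, and power lies between the two sets of figures.

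**What to change.** Reconcile the centre count and the mean per authority across the Abstract, Design, Setting and Sample size, and say which population each count describes. Randomisation is complete according to Trial status, so the number of participating centres, their mean per authority and their CV should be obtainable.

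- If the mean of 6 is confirmed, correct the Setting figure to about 192, or explain why the eight lost authorities contribute no centres.
- If the mean is not 6, recompute Table 1 with the correct mean and CV, and restate the 80% power sentence with the differences actually detectable (about 27.5 to 29 points at ICC 0.05 for 108 centres).

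The cost is a few reworded sentences and at most one recalculated table. Sites, allocation, outcomes and analysis are unaffected.

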### Data collection and transfer

In this trial, we will use routinely collected data for all primary and secondary outcomes, except for the process evaluation data, which will be gathered by an independent LICTR researcher. HENRY has designed a centralised process for evaluating programmes, developed for QA purposes and reporting to commissioners of the service. For the purpose of this trial, baseline data at the centre level include routine data on enrolment and attendance at programmes that have been run before randomisation. These data also include anonymous information on participant satisfaction, parent-reported compliance, parenting and family lifestyle (Table 2), which are gathered in questionnaires on the first and last days of each HENRY programme. This information is submitted to the central HENRY office (without any personal identifiers for the families), which check the data for completeness and collate the information in a.csv file.

**Table 2 Tab2:** Data collection summary

Data	Screening	Randomisation	Baseline	On-going	Follow-up
Local authority level					
Cluster eligibility	X				
Stratification factors		X			
Programme enrolment			X		X
Programme attrition			X		X
Implementation data (e.g., fidelity)				X	
Parent level (anonymised routine)					
Infant diet (fruit and vegetable intake)			X		X
Family habits and lifestyle			X		X
Implementation/process data				X	
Intervention level					
Costs for intervention delivery for economic evaluation	X	X	X	X	X

X indicates when data are gathered

For the trial period, centre-level baseline data from the most recent programme delivered prior to randomisation (winter term 2015) will be used. Follow-up data will be gathered 12 months after randomisation. It will include routine data collected from the autumn and spring terms (2016–17), allowing 6 months for intervention delivery at all sites followed by the delivery of two terms of HENRY programmes. In accordance with the planned intention-to-treat (ITT) analysis, data will be collected from centres that are not compliant with the intervention. For those withdrawing from the trial, only data collected up to the point of withdrawal will be used.

All data transferred from HENRY to the LICTR will be in the form of unlinked, anonymised datasets and will be transferred via a secure, encrypted system. Only data for centres participating in the trial will be transferred. Data transfer agreements (including details on the sender, recipient, content of transfer/general purpose of transfer and any data-processing limitations) will be set up between HENRY and the LICTR prior to the transfer of any data. Queries pertaining to outliers or missing data will be sent to HENRY in accordance with LICTR standard operating procedures. Any new data that are identified following queries will also be transferred via the secure, encrypted system. Missing data, except individual data items collected via parent questionnaires, will be chased until it is received, confirmed as not available, or the trial is at analysis. For missing item-level data within questionnaires (item non-response), no attempts will be made to retrieve missing data; only missing questionnaires will be chased.

All data provided will be stored, handled and processed in accordance with the principles of the 1998 Data Protection Act, the operation of the agreement and the study publication policy. The rights for this data belong to the study sponsor, and no processing, including further data transfer in whole or in part to a third party, is permitted other than as stated in the data transfer agreements.

### Analysis

Statistical analysis of the quantitative elements of the trial is the responsibility of the LICTR statisticians. The analysis plan outlined in this section will be reviewed, and a detailed statistical analysis plan will be written and approved, before any formal analyses are undertaken. Statistical analyses will be carried out by the ITT principle, and statistical significance will be assessed at the two-sided 5% significance level. The ITT population is defined as analysis according to the randomisation and regardless of compliance with the protocol or withdrawal from the trial.

#### Primary analysis

The primary outcomes associated with enrolment or attrition will be compared between the intervention and control arms through a cluster-level analysis, using a weighted *t* test of cluster-level proportions and a two-stage process to adjust for covariates [55]. Intervention effects and corresponding 95% confidence intervals will be presented. As part of a sensitivity analysis, the reliability of random effects logistic regression will also be investigated.

In the primary analyses, missing data will be assumed to be missing completely at random; that is, analyses will be performed using complete cases (including those where sufficient item-level data exists). The extent of unit non-response (data missing from a whole course) will be assessed, and the reason for missingness and the missing data mechanism will be investigated.

A sensitivity analysis accounting for all participants in the ITT population assuming data missing at random, using multiple imputation, will be performed, and potential predictors of missingness will be investigated. The number of imputations will be determined using Bodner rule of thumb, where number of imputations is similar to the percentage of cases that are complete [56].

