There is a need for pragmatic, ‘real-world’ evaluations of interventions to understand the generalisability of the interventions across everyday practice [19, 20]. Further, in order for interventions to be accurately implemented and interpreted, the underpinning behaviour change techniques need to be clearly defined [21]. Implementation optimisation strategies can then be adopted to target a specific intervention component [22]. It is imperative that parent engagement be improved across all parenting interventions delivered in community settings to optimise their impact and so that the degree to which they are effective can be assessed with confidence. In contrast to conventional pathways, in which implementation research is conducted following trials for clinical effectiveness [23], it is argued that there is a need for comprehensive early-phase (evidentiary) evaluation and enhancement of complex interventions such as those designed to prevent childhood obesity [24], prior to the conduct of large randomised controlled trials (RCTs). This novel approach ensures that factors which limit trial outcomes, such as low adherence, are minimised prior to dedicating the resources required to conduct a large trial which may identify no evidence of effectiveness, perhaps as a result of poor compliance.

The present trial involves the evaluation of an implementation enhancement ‘optimisation intervention’ of an existing preschool obesity prevention group programme, HENRY (Health Exercise Nutrition for the Really Young), to promote parent enrolment and attendance prior to establishing its clinical effectiveness and cost-effectiveness. HENRY is an 8-week group-delivered programme provided to parents of preschool children. It was developed in 2006 with joint funds from the Department of Health and the Department for Education (then called the *Department of Children, Schools and Families*) and is currently commissioned and delivered across the United Kingdom by 32 local authorities providing more than 150 programmes each year. It is delivered in community settings, often in children’s centres by children’s centre staff [25]. HENRY uses a responsive approach to provide practical guidance and improve parenting skills aimed at enhancing family lifestyle and children’s centre environments. Preliminary data indicate that HENRY may be effective at preventing childhood obesity and improving family health [25], although there is not yet evidence from an RCT.

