### Exclusion criteria

Local authorities:Local authorities which plan to decommission the HENRY intervention during the period of the trial or which are not planning to run any HENRY programmes during the trial period

Children’s centres:Centres which were recruited in the development phase of the optimisation intervention (participating in the rapid ethnography)Centres which are not planning to run any HENRY programmes during the trial period

There will be no exclusions based on the demographics of children’s centres, but location will be monitored to ensure inclusion of those with diverse social and environmental characteristics. Randomisation will also stratify by area-level deprivation to ensure balance between trial arms.

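### A centre that delivers no programme at follow-up appears to leave the primary comparison, and no planned analysis counts it as missing the target

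*Protocol article*

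**What the plan says.** All references are to the protocol article.

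- **Primary outcome.** There are two co-primary outcomes, both proportions of centres and both defined per programme: enrolling eight or more parents, and having at least three-quarters of parents attend five of the eight sessions.
- **Primary analysis.** For these outcomes "missing data will be assumed to be missing completely at random; that is, analyses will be performed using complete cases". The extent of, and reasons for, a whole course lacking data will be examined. The back-up is "A sensitivity analysis accounting for all participants in the ITT population assuming data missing at random, using multiple imputation".
- **Exclusion criteria.** The centres screened out are "Centres which are not planning to run any HENRY programmes during the trial period". Under Recruitment and consent, this is self-reported.
- **Data collection and transfer.** Follow-up uses the autumn and spring terms of 2016–17. Parent-reported data are those "which are gathered in questionnaires on the first and last days of each HENRY programme".
- **Secondary analysis.** Adherence and the parent-reported outcomes are analysed as for the primary outcomes, and so is the combined enrolment, attrition and adherence target.
- **Analysis.** The intention-to-treat population follows randomisation, whatever happens later with compliance or withdrawal.

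**The concern.** An outcome defined per programme does not exist for a centre that ran none, and the complete-case rule then removes that centre from the denominator. The screening rule concerns plans only, so some randomised centres may plan a programme and not deliver it.

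Whether a programme runs is settled after randomisation. Intervention sites are not blinded (Blinding), and they receive extra support and modified marketing (Intervention). Allocation could therefore change which centres run, in either direction. If it does, missing completely at random fails and the arms are compared on a subset selected after randomisation. That sits poorly with the stated intention-to-treat population.

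Imputation under missing at random does not repair this. It fills in an enrolment and attendance result for an event that did not happen, when the honest description is that no parents were engaged.

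A smaller, parallel problem affects the secondary outcomes built on the last-day questionnaire. Parents who have left by then give no change score, and staying to the end is part of what the intervention tries to alter.

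**Working it through.** **1. Reproducing the plan's own figures.** Inputs from Sample size: 72 centres per arm in 12 local authorities, mean cluster size 6, coefficient of variation 0.54, ICC 0.05 or 0.1, control enrolment rate 55%. From Analysis: "statistical significance will be assessed at the two-sided 5% significance level".

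- Design effect = 1 + [(0.54² + 1) × 6 − 1] × ICC = 1.337 (ICC 0.05) or 1.675 (ICC 0.1).
- Effective n per arm = 72/1.337 = 53.8, or 72/1.675 = 43.0.
- Two-proportion power (pooled variance for the test): 55% to 80% gives 79.9% and 70.3%; Table 1 has 79% and 70%. Attrition, 50% to 75%, gives 77.2% and 67.3%; Table 1 has 76% and 67%.
- All 36 cells of Table 1 agree within 1.4 points.

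Table 1 therefore assumes that all 144 centres contribute, with no allowance for centres without a programme.

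**2. Effect among running centres against effect among all centres.** The non-running shares m are assumptions (10% to 30%); the documents give none. Take success among running centres as 55% (control) and 80% (intervention). Complete cases estimate 80 − 55 = 25 points throughout. Counting non-running centres as not meeting the target gives 80(1 − m_int) − 55(1 − m_con).

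| m control | m intervention | Success among all centres | Difference |
|---|---|---|---|
| 10% | 10% | 72.0 v 49.5 | 22.5 |
| 20% | 20% | 64.0 v 44.0 | 20.0 |
| 30% | 30% | 56.0 v 38.5 | 17.5 |
| 30% | 10% | 72.0 v 38.5 | 33.5 |
| 10% | 30% | 56.0 v 49.5 | 6.5 |

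With no effect among running centres, shares of 30% control and 10% intervention give 49.5 − 38.5 = +11 points for enrolment and 45 − 35 = +10 for attrition. With the shares reversed they give −11 and −10. Complete cases give 0 each time.

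**3. Power of the two analyses.** True effect 55% to 80% among running centres, equal non-running in both arms, method of step 1:

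| Non-running | Complete cases, ICC 0.05 | Failure-scored, ICC 0.05 | Complete cases, ICC 0.1 | Failure-scored, ICC 0.1 |
|---|---|---|---|---|
| 0% | 80% | 80% | 70% | 70% |
| 10% | 77% | 67% | 68% | 57% |
| 20% | 73% | 55% | 65% | 46% |
| 30% | 68.5% | 44% | 61% | 37% |

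**4. Parents without a last-day questionnaire (secondary outcomes only).** Assume 50% adherent among completers in both arms, with 60% of parents completing in control and 75% in intervention. Complete cases: 50 − 50 = 0. Counting the others as not adherent: 0.75 × 50 − 0.60 × 50 = 37.5 − 30 = 7.5 points.

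**The case against.** Several points on the other side stand.

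- **The exclusion of non-running centres is inferred.** The article does not say how such a centre is scored. Its remark on a course without data most naturally means a course that ran but returned nothing, and the detailed analysis plan may settle the matter. What remains is that the article fixes the complete-case rule and a per-programme outcome, and together these give a non-running centre no place.
- **Safeguards exist.** Missing data will be chased, and the reasons, mechanism and predictors of missingness investigated. This would describe the problem, but no stated analysis would act on it.
- **Failure scoring changes the question.** The control rates come from previous programmes. Counting non-running as failure mixes parent engagement with funding and staffing, and it costs power (step 3). That argues for a sensitivity analysis and against replacing the primary one.

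A reader might also infer more than the documents support:

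- *That early leavers drop out of the attrition co-primary outcome.* They do not: a parent with fewer than five sessions counts against the centre there.
- *That programmes are cancelled for low numbers.* Nothing says so, and the assumed 55% control rate leaves 45% of centres with small groups that did run.
- *That half the centres will not run.* The Background has 32 authorities "providing more than 150 programmes each year". Spread evenly, 150 × 24/32 × 2/3 = 75 programmes in two of three terms, against 144 centres. But 150 is a floor, and Setting places about 144 centres in all 32 authorities, which would leave 144 × 24/32 = 108 in 24. Eligible centres must also have supplied data from their latest programme.
- *That the sign of the result will flip.* It can with chosen inputs. Suppose 54 of 72 control centres run and 29.7 succeed, and the intervention adds ten running centres with two successes. Complete cases give 31.7/64 − 29.7/54 = 49.5% − 55.0% = −5.5 points; all centres give 31.7/72 − 29.7/72 = 44.0% − 41.3% = +2.8. None of the assumed counts comes from the documents.

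**Conclusion.** The concern holds in limited form. The stated rule and the per-programme definitions leave a randomised centre with no follow-up programme out of the primary comparison, and the only other missing-data method would impute a result for it. No stated analysis treats it as not having met the target.

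The size cannot be estimated from the documents. With equal assumed non-running of 10% to 30%, the complete-case and all-centre effects differ by 2.5 to 7.5 points for a 25-point effect. With assumed shares of 10% and 30% the all-centre effect is 33.5 or 6.5 points, a gap of 8.5 or 18.5. If few centres fail to run, and equally by arm, the issue is minor.

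For parents, the point is confined to the secondary outcomes that need the last-day questionnaire, including adherence and, through it, the combined target.

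**What to change.** Add to the analysis plan, before any outcome comparison:

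1. State how a randomised centre with no programme in the two follow-up terms is handled. The complete-case analysis may remain primary.
2. Pre-specify a sensitivity analysis of both co-primary outcomes over all randomised participating centres, counting a centre that ran no programme as not meeting the target.
3. Report the proportion of centres running a programme by arm and by reason: lack of parents, against funding, staffing or other.
4. Restrict multiple imputation to programmes that ran but whose data were not returned.
5. For adherence and the combined target, add a sensitivity analysis counting enrolled parents without a last-day questionnaire as not adherent, beside the complete-case figure.

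The cost is wording plus a yes/no record of running and a reason for each centre. The HENRY central office, which collates the programme data, should be able to supply the first; the reason may have to be asked for. The downside is that closures unrelated to parents also count as failures and power is lower, so the result should be read beside the complete-case result and the split by reason. Item 5 likewise makes adherence partly a restatement of retention, which is why it should not stand alone.
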